| TITLE OF STUDY                        | Evaluation of effects of an exercise program on back-health                                                                                                                                                                                                                                                                                                                                                                                                                                                                                                                                                                                                     |
| CONDITION                             | Healthy participants, as well as persons with chronic low back pain.                                                                                                                                                                                                                                                                                                                                                                                                                                                                                                                                                                                            |
| OBJECTIVE(S)                          | Evaluation of effects of a health-insurance initiated program for back-health in companies.                                                                                                                                                                                                                                                                                                                                                                                                                                                                                                                                                                     |
| INTERVENTIONS(S)                      | 
Intervention:
Structured training to strengthen (vitalize) back muscles (3 days per week for 20 min.) over a period of 20 weeks.
 
Control group:
20 weeks no intervention as waiting-control group, followed by a training intervention over a period of 20 weeks (see intervention)
 
Duration of intervention per patient:
20 weeks
 
Follow-up per patient
Not intended
                                                                                                                                                                                                                   |
| KEY INCLUSION AND EXCLUSION CRITERIA  | 
Inclusion criteria:
 
 
- Male and female
 
- Age: <math>\geq 18</math> to 67 years
 
 
Exclusion criteria:
 
 
- Actual participation of training for back-health
 
- Known alcohol or drug abuse
 
- Diseases which exclude a participation
 
- Clinical relevant, acute or chronic infections
 
- Pregnant women
 
                                                                                                                                                                                      |
| OUTCOME(S)                            | 
Primary endpoint:
 
 
- Isometric low back strength (newton meter in 0 degree extension)
 
 
Key secondary endpoints:
 
 
- Isometric strength of lateral flexion
 
- Change of back pain score with the Oswestry Low Back Pain Disability Questionnaire (OBQ)
 
- Visual analog scale (VAS)
 
- Evaluation of the health-related quality of life by the questionnaire SF-36
 
- Work-Ability-Index
 
- "Freiburger" activity questionnaire
 
- Sick days
 
 
Documentation for safety:
 |

|                              |                                                                                                                                                                                                                                                                                                                                                                                                                                                                                                                                                                                                                                                                                                                                                                                                                                                                                                                                                                                                                                                                                                                                                                                                                                                                                                |
|------------------------------|------------------------------------------------------------------------------------------------------------------------------------------------------------------------------------------------------------------------------------------------------------------------------------------------------------------------------------------------------------------------------------------------------------------------------------------------------------------------------------------------------------------------------------------------------------------------------------------------------------------------------------------------------------------------------------------------------------------------------------------------------------------------------------------------------------------------------------------------------------------------------------------------------------------------------------------------------------------------------------------------------------------------------------------------------------------------------------------------------------------------------------------------------------------------------------------------------------------------------------------------------------------------------------------------|
|                              | Documentation of any serious events                                                                                                                                                                                                                                                                                                                                                                                                                                                                                                                                                                                                                                                                                                                                                                                                                                                                                                                                                                                                                                                                                                                                                                                                                                                            |
| STUDY TYPE            | Prospective, randomized and controlled study.                                                                                                                                                                                                                                                                                                                                                                                                                                                                                                                                                                                                                                                                                                                                                                                                                                                                                                                                                                                                                                                                                                                                                                                                                                                  |
| STATISTICAL ANALYSIS  | 
Effectivity:
The primary goal of the study is to show that a structured training to strengthen the back-muscles over 20 weeks results in an improvement of isometric low back strength in comparison to the control group. The two-sided type1 error is defined as 5%.
 
Description of the statistic evaluation of the primary endpoint
The primary evaluation is carried out in the intention-to-treat (ITT) population. For back strength in newton meter an ANCOVA-Model will be used with the before-after difference as dependent-variable. Important co-variables are baseline strength, the group (intervention or control), low-back pain (yes/no) as well as the company. The intervention is successful, if the lower mark of the two-sided 95%-confidence interval is bigger than 0.
 
Secondary endpoints
The most important secondary endpoints will be evaluated as the primary endpoint. For dichotomic endpoints a logistic regression will be used and adjusted for the same co-variables. 95%-confidence interval will be calculated for all secondary endpoints.
 
Safety and incidences
Any unexpected event of randomized participants will be captured and descriptively compared between the groups.
 |
| SAMPLE SIZE           | 
Tested for eligibility: n = 250 per group
 
Randomized for participation: n = 200 per group
 
To analyze : n = 200 per group
                                                                                                                                                                                                                                                                                                                                                                                                                                                                                                                                                                                                                                                                                                                                                                                                                                                                                                                                                                                                                                                                                                        |
| TRIAL DURATION        | 
Duration first participant in and last participant out(weeks): 50
 
Duration of whole study (weeks): 52
 
Recruiting period (weeks): 10
                                                                                                                                                                                                                                                                                                                                                                                                                                                                                                                                                                                                                                                                                                                                                                                                                                                                                                                                                                                                                                                                                                                  |
| PARTICIPATING CENTRES | 
Participating companies = 3
 
Study administration: Institute of Sports Medicine, MHH
                                                                                                                                                                                                                                                                                                                                                                                                                                                                                                                                                                                                                                                                                                                                                                                                                                                                                                                                                                                                                                                                                                                                                                                              |

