##### Key secondary endpoints:

- Isometric strength of lateral flexion to the left and right
- modification of dorsalgia with help of the Oswestry low back pain disability questionnaire (OBQ)
- Visual analog scale (VAS)
- Determination of the health claiming life quality by using the questionnaire SF-36
- Work-Ability-Index
- Freiburger activity questionnaire
- sick days

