### Safety Analysis

Unexpected events will be documented as absolute und relative numbers. The comparison of groups will be analyzed with the Chi-quadrat test and p-values will be considered descriptively.

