## **5. ETHICAL CONSIDERATIONS**

There are no specific risks by the conduction of this study.

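### The safety event class is set as serious events in the outcome list and as unexpected events in the analysis, with neither term defined, so what the harm comparison counts is left to individual judgement

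*Protocol*

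**What the plan says.** The Protocol deals with safety in four places.

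- **Synopsis, OUTCOME(S).** Under the label "Documentation for safety" the single entry is "Documentation of any serious events".
- **Synopsis, STATISTICAL ANALYSIS, safety paragraph.** "Any unexpected event of randomized participants will be captured and descriptively compared between the groups". Nothing here limits the events by seriousness.
- **Section 4, Safety Analysis.** "Unexpected events will be documented as absolute und relative numbers". The method follows: "The comparison of groups will be analyzed with the Chi-quadrat test and p-values will be considered descriptively".
- **Section 5, Ethical Considerations.** "There are no specific risks by the conduction of this study".

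The Protocol defines neither serious nor unexpected, and it contains no list of expected events. Pain and function also appear as efficacy measures: the Oswestry questionnaire, the visual analog scale and sick days are key secondary endpoints (Section 3.3). Section 4 (Design) places the secondary endpoints before and after the intervention in both groups.

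**The concern.** The set of events to be documented and the set to be compared are described by different attributes. The trial enrols healthy employees and people with chronic low back pain, and asks them to do back exercises largely on their own. New or worse back pain and muscle strain are plausible harms of such a programme, and they would often not be serious. Whether they count as unexpected is a matter of opinion unless the Protocol says so.

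At stake is the only planned between-group comparison of harm. If the event class is not fixed, a similar count in both groups could reflect how events were classified as much as what the training did, and a difference could arise in the same way.

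**Working it through.** The Protocol gives no event rate or safety figure to reproduce, so the check is a comparison of the stated rules.

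**Step 1: cross the two attributes.**

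| Event | In the outcome list (serious) | Captured and compared in the analysis (unexpected) |
|---|---|---|
| Serious, unexpected | yes | yes |
| Serious, expected | yes | no |
| Not serious, unexpected | no | yes |
| Not serious, expected | no | no |

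The two rules agree on inclusion in the first row only. In the second row an event is documented but not compared. In the third it is compared although the outcome list does not name it. The fourth row lies outside both.

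**Step 2: place a back-pain flare or strain in the table.** If it is not serious, it belongs in row three or row four, depending on whether it is called expected. The Protocol does not settle this. Section 5 names no specific risk, which favours unexpected. A form-filler who knows that training can cause soreness may choose expected.

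**Step 3: what this does to the comparison.** Let p_T and p_C be the true proportions with a flare or strain in the training and control groups, and s_T and s_C the shares of these that are noticed and classed as unexpected. The recorded difference is

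s_T × p_T − s_C × p_C.

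- With s_T = s_C = 1, it equals the true difference p_T − p_C.
- With s_T = s_C = 0, nothing is recorded.
- With equal shares in between, the difference is shrunk by the common factor s.
- With unequal shares, it can be biased in either direction.

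The Protocol fixes neither share, so each can lie anywhere from 0 to 1.

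**Step 4: opportunity to notice events.** The training is 3 days per week for 20 weeks, so 3 × 20 = 60 sessions. Section 3.1 describes trainer meetings once per month; counting a month as four weeks, that is about 20 / 4 = 5 meetings. These are described for the intervention group only. No contact with the control group between the two assessments is described, so s_T and s_C may well differ.

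**Step 5: do the efficacy measures fill the gap?** Partly. Worsening still present at week 20 would show in the Oswestry questionnaire or the visual analog scale. A flare that begins and resolves between the two assessments would not be captured by a before-and-after design. Sick days would reflect only events that led to absence, and the Protocol does not assign them to a cause.

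**The case against.** A reader might infer that pain flares are bound to go unrecorded, that the harm comparison must come out close to zero, and that the safety rules could never contradict Section 5. The documents do not support this. That inference needs a flare to be classed as expected, and the Protocol lists no expected events. A document that foresees no specific risk gives no firm ground for excluding a flare as foreseen. The synopsis analysis row would then capture it in any randomized participant, with no seriousness limit, and the resulting table could contradict Section 5.

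Four further points deserve weight.

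- The outcome list does not say that only serious events are recorded, and the analysis row is worded as a collection rule as well as an analysis rule. The two can be read as complementary. This softens the mismatch, but the union of the two rules still omits expected non-serious events and still leaves serious expected events out of the comparison.
- Pain, disability and sick days are measured in both groups, so persistent harm would not be invisible. This stands. It does not cover transient events.
- The text reads in places like a translation from German, and unexpected event may be a loose rendering of adverse event. The document cannot confirm this. If so, the correction is small, but it is still needed because the outcome list says serious.
- Detailed definitions may sit in an analysis plan or in collection forms that are not shown. That is reasonable for detail. Here, however, the Protocol itself states the class of events, and does so in two ways. An analysis plan cannot recover events that were never collected.

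**Conclusion.** The inconsistency is real and is visible in the text: serious in the outcome list, unexpected in both analysis statements, and neither defined. Its size cannot be put as a number, because the Protocol gives no event rates. What can be said is that the recorded share of non-serious flares and strains could be anything from none to all, and that this share could differ between arms. The conclusion rests on a literal reading of the two terms and on the absence of any list of expected events. It does not rest on any assumed rate of harm.

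The primary endpoint and its analysis are unaffected. The change should still be made before data are collected, because as written the only planned comparison of harm cannot be interpreted with confidence in either direction.

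**What to change.** Use one event class in the synopsis outcome list, the synopsis analysis row and the Safety Analysis in Section 4: all adverse events in randomized participants, regardless of seriousness or expectedness, explicitly including new or worsened back pain and strain. Collect them with the same question, at the same times, in both arms. Compare the number of participants with at least one event, keeping the chi-square test and descriptive p-values already planned, and list serious events as a subset. Revise the sentence in Section 5 so that it agrees with this definition.

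The cost is protocol wording and one event question on the form. Because no interim contact with the control group is described, equal collection means either asking both arms at the closing assessment about the whole 20 weeks, with some loss of recall, or adding a brief contact in both arms. The downside is more minor events to record and a less favourable-looking safety table.

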### 3.5 PROPOSED SAMPLE SIZE / POWER CALCULATIONS

The primary goal of the study is to show that an improvement of the isometric low back strength can be achieved after 20 weeks of training. The back strength is measured in newton meter, in which case high values are positive. By looking at the after-before differences, positive trunk strength-differences indicate an improvement of the functional back health. We plan to include 200 volunteers. Therefore the planning is calculated in nQuery Advisor 7.0, which effect could be shown by given number of subjects. The number of evaluable patients is based on data of an prospective, randomized study with 21 volunteers from Moon HJ et al., Ann Rehabil Med., 2013, 37(1): 110-117, in which two intervention methods are being executed on patients with chronic back pain for a period of eight weeks. In the group with a similar training comparable to the planned intervention a mean improvement from 104.0 (sd=42.5) to 135.2 (sd=75.9) could be observed. Assuming that the control group remains similar and both groups start with the same baseline-values (average= 104.0), it comes to the result that with a t-test for same variances (bigger variance to conservative planning (sd= 75.9)), a 1. Type error of 5 % (double sided) and a power of 80%, an improvement up to 134.22 Newton meter can be expected. This correlates roughly to the change which Moon et al. has been shown and is considered relevantly so that the number of cases can be considered as adequate.

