### 3.6 FEASIBILITY OF RECRUITMENT

The recruiting of volunteers for the AOK prevention program for back health will take place in three companies over an internal informative events and internal advertisement. The number of employees in these companies is all in all about 2000 employees. Due to the expectedly positive effects of the event and the degree of esteem of training to strengthen the musculoskeletal system, we are not expecting any problems referring to the recruitment. We expect that the planned 200 volunteers will be recruited.

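### The synopsis gives 200 participants per group, but the sample-size calculation and the feasibility argument support 200 altogether, 100 per group

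*Protocol*

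**What the plan says.** The sample-size row of the Protocol synopsis lists "n = 250 per group" tested for eligibility, then "n = 200 per group" twice, once as randomized and once as analysed. With two groups that is 500 screened and 400 randomized.

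Section 3.5 opens its calculation with "We plan to include 200 volunteers" and asks what effect that number can show. It concludes that "an improvement up to 134.22 Newton meter can be expected". Section 3.6 repeats the number: "We expect that the planned 200 volunteers will be recruited", out of about 2000 employees in three companies. Section 4 (Design) fixes 1:1 allocation after screening. No section reconciles 200 per group with 200 volunteers.

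**The concern.** The number to randomize is a core design figure, and the protocol gives two values that differ by a factor of two. Three things depend on which one applies:

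- **Detectable effect.** Section 3.5 calls the sample size adequate because the detectable mean is close to the one seen in the cited eight-week study. That argument belongs to one sample size only.
- **Recruitment.** Section 3.6 argues feasibility for 200 people, not for 400.
- **End of enrolment.** Stopping at 200 and continuing to 400 would each agree with part of the protocol. A later reader could not tell whether the final number was planned or chosen along the way.

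**Working it through.** **Inputs, all from Section 3.5 unless noted**

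- Test: two-sample t-test with equal variances.
- Type I error 5% two-sided, power 80%.
- Mean at baseline: "both groups start with the same baseline-values (average= 104.0"), with the control group assumed to stay there.
- Common SD: "bigger variance to conservative planning (sd= 75.9").
- Stated result: 134.22 Nm. This is the mean reached in the intervention group, since the text compares it with 135.2 Nm in the cited study. The difference is 134.22 − 104.0 = 30.22 Nm.
- Allocation 1:1 (Section 4).

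**Formula**

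With n per group, the standard error of the difference is SE = SD × √(2/n). The detectable difference δ is the value at which a noncentral t with 2n − 2 degrees of freedom and noncentrality δ/SE exceeds the two-sided 5% critical value with probability 0.80. The normal approximation is δ ≈ SE × (1.960 + 0.842).

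**Step 1: reproduce the stated figure with 100 per group**

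- SE = 75.9 × √(2/100) = 10.73 Nm.
- Normal approximation: δ ≈ 30.07 Nm.
- Noncentral t: δ = 30.219 Nm, so the detectable mean is 104.0 + 30.219 = 134.22 Nm.

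This matches the protocol to two decimals. The match is sharp: 99 per group gives 134.37 Nm and 101 per group gives 134.07 Nm.

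**Step 2: the same calculation with the synopsis figure, 200 per group**

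- SE = 75.9 × √(2/200) = 7.59 Nm.
- Noncentral t: δ = 21.32 Nm, so the detectable mean is 125.32 Nm.
- Power at the stated difference of 30.22 Nm (noncentrality 30.22/7.59 = 3.98): 97.8%, not 80%.

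**Step 3: can another reading rescue 200 per group?**

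| Variant at 200 per group | Detectable mean (Nm) |
|---|---|
| Stated inputs | 125.32 |
| One-sided 5% | 122.90 |
| SD 42.5 (the cited study's baseline SD) | 115.94 |
| SD 61.5 = √((42.5² + 75.9²)/2) | 121.27 |
| 90% power | 128.66 |

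None gives 134.22. To reach it with 200 per group the SD would have to be 75.9 × 30.22/21.32 ≈ 107.6, a figure that appears nowhere in the protocol.

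**Step 4: what each reading asks of recruitment**

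| | Sections 3.5 and 3.6 | Synopsis |
|---|---|---|
| Randomized | 200 | 400 |
| Share of about 2000 employees | 10% | 20% |
| Per week over the 10-week recruiting period | 20 | 40 |
| Screened | not stated | 500 (25% of employees) |

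**The case against.** Sections 3.5 and 3.6 never say that 200 is a total; that is inferred. This is fair as a remark on wording, but 200 volunteers to be included, split 1:1, is most naturally 200 overall, and the exact match at 100 per group settles it.

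Neither reading leaves the trial short of power on its own assumptions: power at 30.22 Nm is 80% with 200 people and 97.8% with 400. This also stands. The defect does not make the primary analysis invalid or inflate its error rate. The protocol describes no interim look and sets a fixed recruiting period, so a data-driven choice of stopping point is a possibility the ambiguity leaves open, not something the plan provides for.

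The participation shares do not show that 400 is infeasible, because no expected uptake is given. They show only that the case was made for 200.

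Finally, the 21.32 Nm figure comes from the protocol's simple t-test with a post-treatment SD, whereas the planned analysis is an ANCOVA of the change adjusted for baseline. The figure is right as a restatement of Section 3.5, but it is not the detectable effect of the planned analysis.

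None of these points reconciles the synopsis with Sections 3.5 and 3.6.

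**Conclusion.** The concern holds. The synopsis states 400 randomized, twice the number that the only sample-size justification supports. The calculation in Section 3.5 is arithmetically correct for 100 per group and cannot be obtained with 200 per group from any inputs in the protocol. The gap is 30.22 against 21.32 Nm in detectable difference at 80% power, or 80% against 97.8% power at 30.22 Nm.

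This rests on taking the inputs of Section 3.5 at face value and on equal allocation. The calculation shows which number was used for planning; it cannot show which number the sponsor finally intends. The contradiction must be resolved because it concerns the enrolment target itself.

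**What to change.** State one total and one per-group number, identical in the synopsis, Section 3.5 and Section 3.6.

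- **If 200 in total is intended**, as the calculation indicates: change the synopsis to 100 per group randomized and 100 per group analysed (200 in total). Give the number screened as one total on the same basis, since participants are screened before any group exists. Add to Section 3.5 that 200 is the total, 100 per group. Cost: the three figures in one synopsis row and a few words in Section 3.5, with no extra participants.
- **If 400 is intended**: restate Section 3.5 as 200 per group with a detectable difference of 21.3 Nm under the same t-test assumptions (or 97.8% power at 30.22 Nm). Rewrite the adequacy argument accordingly, and redo Section 3.6 for 400 randomized and 500 screened. Cost: two sections rewritten and 200 more participants than those sections now support.

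Whichever applies, record the decision in a dated amendment, before outcome data are examined, so that the final number can be seen to have been planned.
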